#### Effectiveness

Adolescents’ heights and weights are to be measured to determine BMI at all follow-up timepoints along with an assessment of eating disorder symptoms using the EDE and the Eating Disorder Inventory (EDI-2; [34]). Both instruments have excellent reliability and validity [7, 12]. The primary outcomes for adolescents are improvement in BMI *z*-score based on the CDC growth charts, as well as a decrease in eating-related psychopathology. Secondary endpoints include stabilization of somatic health status, as measured by vital signs (blood pressure and pulse), improvement in psychosocial well-being and reduction in perceived stress. Accordingly, parents will complete the Perceived Stress Scale (PSS; [5]), which is commonly used to quantify subjective feelings of stress. Adolescents will also complete the Brief Dyadic Scale of Expressed Emotion (BDSEE; German translation by [32]), which captures expressed emotions from the patient’s perspective.

#### Interfamily relations as mediator/moderator

In order to examine how perceived intrafamily stress affects different treatment schemes, at the beginning of treatment and at follow-up assessments, both adolescents and parents are to be interviewed using the short version of the Family Questionnaire (FB-K; German translation, Familienbogen–Kurzversion; [4], a self-report instrument used to assess family function in relation to two aspects: (1) emotional connection between family members and (2) willingness to communicate.

### Power analysis

The target sample size for the primary analysis was derived from an a priori power calculation using G*Power (version 3.1.9.7) and repeated measures ANOVA as a statistical model. Assuming a small effect size of *f* = 0.2, power of 80%, type 1 error level of *p* < 0.05 and correlation among repeated measures of *r* = 0.5, the necessary total sample size of 66 is adequate to test our main hypothesis involving three groups, two time points and the statistical interaction term. Assuming a reasonable attrition rate of 25%, we set our target sample to 90, equivalent to 30 participants per group, assuming equal treatment arm sizes. This number also aligns with the study feasibility, as it approximates the number of eligible patients who previously registered at the outpatient clinic over time intervals similar to the planned recruitment period of 3 years.

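### The effect labelled small (f = 0.2) implies a largest between-arm difference in change of 0.85 to 0.98 SD, and the 80% is omnibus power, not power to beat both comparators

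*Protocol article*

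**What the plan says.** The Power analysis section of the protocol article uses "G*Power (version 3.1.9.7) and repeated measures ANOVA as a statistical model". Its effect size and power are given as "Assuming a small effect size of *f* = 0.2, power of 80"%. Alpha is set at 0.05, and the two measurements on a participant are taken to correlate at 0.5. It says that "the necessary total sample size of 66 is adequate to test our main hypothesis", for "three groups, two time points and the statistical interaction term". Allowing for 25% attrition, the target is set at 90, or 30 per arm.

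The Introduction gives the main hypothesis: FBT-HT does better than both FBT alone and FBT-MBSR on weight and on eating disorder psychopathology. The Data analysis plan tests the primary outcomes by repeated measures ANOVA and, if there is a significant effect, by Tukey comparisons of the treatment means. The article does not translate f = 0.2 into a difference between arms on BMI z-score, EDE or EDI-2.

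**The concern.** G*Power offers more than one definition of f for a group-by-time interaction, and the same number can stand for very different differences between arms. Under the definition that yields 66, f = 0.2 appears to be a large between-arm difference. The article would then be claiming 80% power for small effects when the design lacks it.

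The 80% also belongs to the three-group omnibus test, whereas the hypothesis needs FBT-HT to win two pairwise comparisons. A reader who takes the section at face value could read a non-significant result as evidence against small or moderate benefit. The same reader could plan the subsequent confirmatory study, which the Data analysis plan mentions, on a false idea of what this trial could detect.

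**Working it through.** **Inputs from the Power analysis section:** f = 0.2, alpha = 0.05, r = 0.5, k = 3 groups, m = 2 time points, interaction term, N = 66 (22 per arm), target 90.

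**1. Reproduce the 66.** The default within-between option uses a noncentral F with lambda = f² × N × m / (1 − r), df1 = (k − 1)(m − 1) and df2 = (N − k)(m − 1).
- lambda = 0.04 × 66 × 2 / 0.5 = 10.56, with F(2, 63). Power is 0.818.
- The smallest N with equal arms that reaches 80% is 66.
- With the *as in SPSS* option the same inputs need 249. With f defined directly on change scores (lambda = f² × N) they need 246.
- Only the default option gives 66, so the stated N identifies which f was used.
- Attrition: 66 / 0.75 = 88, so 90 is consistent.

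**2. Translate f into a difference between arms.** With two time points each interaction cell effect is half of a group's deviation in mean change, so f = SD(group mean changes) / (2 × SD of the outcome). Hence f = 0.2 means that the group mean changes have an SD of 0.4 outcome SDs. At r = 0.5 the SD of change is √(2 × (1 − 0.5)) = 1 outcome SD, so this is f = 0.4 on the change score.
- FBT-HT ahead of two equal comparators by d: SD of the changes = d√2/3, so d = 0.4 × 3/√2 = 0.85 SD.
- Evenly graded arms (0, d/2, d): SD of the changes = d/√6, so d = 0.4 × √6 = 0.98 SD. FBT-HT is then 0.98 SD above one comparator and 0.49 SD above the other.
- Intermediate example: gaps of 0.94 and 0.71 SD.

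Across all patterns the largest pairwise gap lies between 0.85 and 0.98 SD.

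**3. Omnibus power for a common gap d over both comparators** (f = d√2/6, N = 66, r = 0.5):

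| d (SD) | Omnibus power | N for 80% |
|---|---|---|
| 0.2 | 9% | 1089 |
| 0.3 | 16% | 486 |
| 0.5 | 37% | 177 |
| 0.6 | 51% | 126 |
| 0.85 | 82% | 66 |

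**4. Sensitivity.** Values of r other than 0.5 are assumptions.
- Power at 0.5 SD: 49% if all 90 are observed (r = 0.5); with 66, 57% at r = 0.7 and 76% at r = 0.8.
- Common gap giving 80% omnibus power with 66: 0.98 SD at r = 0.3, 0.83 at r = 0.5, 0.64 at r = 0.7 and 0.53 at r = 0.8. With all 90 observed and r = 0.5 it is 0.71 SD.

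**5. Power for the stated hypothesis.** This is a simulation of the change scores with 22 per arm, equal comparators, r = 0.5 and Tukey comparisons at 5%. Tukey is taken to apply to the pairwise differences in change.

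| Gap over both (SD) | One given comparison | Both comparisons |
|---|---|---|
| 0.5 | 24% | 11% |
| 0.85 | 66% | 51% |
| 1.08 | 88% | 80% |

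**6. Precision.** The studentized range critical value for 3 means and 63 df is 3.39, so the simultaneous 95% half-width is 3.39 / √22 = 0.72 SD. The unadjusted half-width, 0.60 SD, does not match the planned Tukey comparisons.

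**The case against.** The strongest defence is that nothing has been miscalculated. The 66 and the 90 follow from the stated inputs, and the fault is one adjective and a missing translation. That stands as far as the arithmetic goes. But the adjective describes what the trial can detect and is attached to a claim of adequacy, and both fail against the article's own inputs.

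A second defence is that 37% is one scenario. This also stands: a higher correlation, or less loss than planned, raises power, and the planned maximum likelihood handling means that dropouts need not contribute nothing. Even so, at r = 0.8 the gap detectable with 66 is 0.53 SD, which is still not small.

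Third, the article nowhere says that a null result would exclude small benefits, and the Data analysis plan already provides for Hedges's g with reference to 95% confidence intervals. The risk of misreading is therefore partly contained.

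A reader might be tempted by two stronger readings:
- *FBT-HT must exceed each comparator by at least 0.85 SD.* This holds only if the comparators are equal. The graded pattern above has f = 0.2 with one gap of 0.49 SD. The 0.85 SD is a floor for the largest pairwise gap only.
- *The target presumes that nearly every eligible patient consents*, because the article says of the 90 that "it approximates the number of eligible patients who previously registered at the outpatient clinic". That sentence is a feasibility remark. The article gives no consent rate and does not say that recruitment stops at that number, so any resulting loss of power would rest on rates supplied from outside.

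**Conclusion.** The label and the adequacy claim are wrong as written; the sample size arithmetic is not. Under the only option tried that yields 66, f = 0.2 corresponds to a largest between-arm difference in change of 0.85 to 0.98 SD. The 80% does not apply to small or moderate differences, nor to superiority over both comparators even at the assumed effect.

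The conclusion rests on the article's own alpha, r = 0.5, three groups and two time points, on 66 analysed, and, for the common-gap figures, on equal comparators. Calling 0.85 SD large is a statement on the SD scale. The documents give no outcome SD or minimal important difference, so they do not show which differences would be clinically relevant.

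**What to change.** Reword the Power analysis paragraph as follows:
- Delete the word small.
- State that f = 0.2 (G*Power default option, r = 0.5) corresponds to about 0.85 SD over both comparators if these are equal. Give and justify what this means for each primary outcome.
- State that the 80% is power for the omnibus interaction test only.
- Add omnibus power at 0.5 SD (about 37% with 66 analysed), power to show superiority to both comparators at 0.85 SD (about 51%), and the Tukey half-width (about 0.72 SD with 22 per arm).
- State that a non-significant result will not be interpreted as excluding small or moderate benefit, and that conclusions will draw on the estimates and intervals already planned.

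The cost is one paragraph of text and less favourable published figures. Enrolment, design and analysis stay as they are.

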The purpose of the proposed study (randomized clinical trial) is to compare the three outpatient treatments (FBT, FBT-HT, FBT-MBSR) for adolescents with AN. We hypothesize that FBT-HT is acceptable, appropriate and feasible and, importantly, outperforms both established FBT alone and FBT supplemented with mindfulness-based stress reduction training (FBT-MBSR) in terms of adolescent weight gain and eating disorder psychopathology. Our primary endpoint is remission of AN symptoms, defined as an increase in body weight as measured by BMI, and a decrease in eating disorder pathology as measured by the Eating Disorder Examination (EDE) total score and EDI-2 total score. Secondary endpoints include stabilization of somatic health status, as measured by vital signs, as well as an improvement in psychosocial well-being and reduction in perceived stress. We hypothesize that FBT-HT will lead to stress reduction in caregivers as well as improvement in interfamily relationships and regulation of perceived and expressed emotions within the family. In addition, we expect that balanced and relaxed family dynamics (integrated in further exploratory analyses as a mediator/moderator variable) will lead to increased effectiveness of FBT and thus improved patient-related outcomes.

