### Data analysis plan

The initial descriptive statistics will summarize participant data characteristics as means, standard deviations, minima, maxima, frequencies and percentages. The validity of stratified randomization will be evaluated by inspecting between-group differences at baseline by means of a one-way analysis of variance (ANOVA), Kruskall–Wallis test or chi-squared test (in dependency of conventional statistical assumptions and the variable type, i.e., continuous versus categorical). Outcome data will be evaluated for the normality assumption by a combination of visual (Q–Q plots, histograms) and statistical (Shapiro–Wilk test) methods and will be transformed if necessary to meet the normality assumption. Participant characteristics of the analyzed sample and dropouts will be subjected to an additional inspection for possible non-random differences. Missing data will be handled by the maximum likelihood estimation method. The effects of the interventions will be assessed as changes in the primary outcomes from pre-test to post-test and follow-up assessment using EDE, EDI-2 and BMI analyzed with a repeated measures ANOVA followed by a post-hoc Tukey’s test to compare treatment means when there is a significant effect. The potential influence of confounding factors (age, premorbid BMI, duration of illness, age at onset, duration and setting of pre-treatment, medication use) will be further explored in sensitivity analyses. The secondary continuous variables will be analyzed in parallel. The measures related to treatment implementation (FBB, BPT) will be evaluated using descriptive statistics. Corrected effect sizes, expressed as Hedges’s *g* and significant deviations beyond the 95% confidence interval, will be computed for between- and within-group terms and will indicate empirical power estimates for a subsequent confirmatory study. Exploratory analyses will test the FB-K measure as a mediator/moderator of efficacy. To examine the FBT process, the ratings of each therapy session by the adolescents and the therapists will be compared and analyzed to assess their common development over time. More advanced statistical methods, such as generalized estimating equations (GEE) (which allow for more flexible modelling of the correlation structure among observations, are less sensitive to violation of assumptions and estimate population-wide average effects) will be also applied to assess differences in BMI percentiles and EDE/EDI-2 trajectories. The statistical significance threshold will be set to *p* < 0.05.

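### The stated 80% power belongs to an omnibus group-by-time test on one outcome; for the main hypothesis, that FBT-HT beats both other arms, the planned Tukey follow-up has about 51% power if the comparators are equal and 22% if FBT-MBSR is halfway

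*Protocol article*

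**What the plan says.** **Hypothesis.** The Introduction expects that FBT-HT "outperforms both established FBT alone and FBT supplemented with mindfulness-based stress reduction training (FBT-MBSR") on weight gain and eating disorder psychopathology. The Discussion part of the Abstract says the same. BMI, EDE and EDI-2 are all listed as primary outcomes in Table 1.

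**Power.** The Power analysis section uses a repeated measures ANOVA, "Assuming a small effect size of *f* = 0.2", 80% power, "type 1 error level of *p* < 0.05" and "correlation among repeated measures of *r* = 0.5". It concludes that "the necessary total sample size of 66 is adequate to test our main hypothesis involving three groups, two time points" and the interaction term. The target becomes 90 (30 per arm) after allowing for 25% attrition.

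**Analysis.** The Data analysis plan assesses effects as "changes in the primary outcomes from pre-test to post-test and follow-up assessment" by repeated measures ANOVA, followed by a post-hoc Tukey "test to compare treatment means when there is a significant effect". It gives no power for any pairwise comparison.

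**The concern.** Outperforming both arms takes two specific wins. The interaction test with 2 degrees of freedom can be significant when only one of them is there, or when FBT-HT is not the arm that stands out. The sentence that calls 66 adequate for the main hypothesis therefore credits the trial with a power that belongs to a different question.

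This matters most for the comparison that justifies the third arm. The Introduction notes that earlier work could not rule out that home-based care does better only because of a more intense therapeutic relationship, for example through added contact time. If that explanation were true, FBT-HT and FBT-MBSR would do equally well and both would beat FBT. The trial would then very likely report a significant interaction although its main hypothesis was false. If the hypothesis is true, the planned follow-up may well miss it.

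**Working it through.** **1. Reproducing the plan's figure.** Inputs from the Power analysis section: f = 0.2, r = 0.5, alpha 0.05, three groups, m = 2 time points. For the within-between interaction:

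- Noncentrality = f² × N × m/(1 − r) = 0.04 × N × 2/0.5 = 0.16N, with 2 and N − 3 degrees of freedom.
- N = 63 gives 79.8% and N = 66 gives 81.8%, so 66 is the smallest equal-arm total that reaches 80%.
- 66/0.75 = 88, so 90 is consistent. Conversely 90 × 0.75 = 67.5 expected completers.

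**2. What f = 0.2 means for arm differences.** With outcome SD 1 and r = 0.5, the SD of change is √(2 × (1 − 0.5)) = 1. The noncentrality 0.16N then corresponds to an SD of √0.16 = 0.4 among the three mean changes. Three patterns with exactly this spread:

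- *Comparators equal:* FBT-HT ahead of both by 0.4 × 3/√2 = 0.849 SD.
- *FBT-MBSR halfway:* steps of 0.4/√(2/3) = 0.490 SD, so FBT-HT leads FBT-MBSR by 0.490 and FBT by 0.980.
- *FBT-HT equal to FBT-MBSR:* both ahead of FBT by 0.849 SD.

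**3. Power of the planned follow-up, 22 per arm.** The standard error of a difference in mean change is √(2/22) = 0.302. The Tukey critical value on the t scale is 2.40 (63 df). With equal comparators the expected ratio is 0.849/0.302 = 2.81, which gives 66% for each single comparison. The joint probability was simulated (1,000,000 trials per pattern), with Tukey applied to change after a significant omnibus test:

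| Pattern | Omnibus significant | FBT-HT beats both (Tukey) |
|---|---|---|
| Comparators equal | 82% | 51% |
| FBT-MBSR halfway | 82% | 22% |
| FBT-HT equals FBT-MBSR | 82% | 1% (false claim) |

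Between the first two rows, joint power is 50%, 46%, 39% and 31% when the middle arm lies 10%, 20%, 30% and 40% of the way up from the lowest arm. Of the omnibus-significant trials, 1 − 51.2/81.8 = 37% fail to show both wins with equal comparators, and 1 − 21.8/81.8 = 73% fail in the halfway pattern.

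**4. Sensitivity to completers.** With equal comparators, joint Tukey power is 54% at 23 per arm and 71% at 30 per arm (no attrition). In the halfway pattern at 30 per arm it is 31%. Reaching 80% with equal comparators takes about 36 completers per arm (108 in total; 108/0.75 = 144 enrolled).

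**5. Two planned contrasts instead, 22 per arm.** Both must have two-sided p < 0.05:

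- *On change, no baseline covariate:* 68% with equal comparators, 35% halfway.
- *Adjusted for the baseline value:* the residual SD falls to √(1 − 0.5²) = 0.866, the standard error to about 0.261, and the expected ratio rises to 0.849/0.261 = 3.25. Simulated joint power is 81% with equal comparators and 44% halfway.

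**The case against.** **Omnibus-then-Tukey is valid.** Tukey protects the error rate over all pairs and does show which arms differ, and FBT versus FBT-MBSR bears on the question of added contact. The plan also mentions a later confirmatory study and supportive GEE models. All of this stands: the sequence does not inflate false claims, and the third pair is not pointless. But the Power analysis section still says that 66 is adequate for the main hypothesis, and that is not so.

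**51% is not a fixed ceiling.** It depends on f = 0.2 and 22 completers per arm. The expected 67.5 completers give 51% to 54%. Maximum likelihood may recover some information from dropouts, but even with no attrition the figure is 71%.

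**Three stronger readings are tempting and not supported.**

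- A reader might infer that Tukey will be applied to means averaged over baseline and follow-up, which would dilute a week-12 effect and leave 11% joint power (comparators equal). The same sentence of the plan speaks of changes in the outcomes, so this is one possible reading only. The 51% uses the kinder one.
- A reader might infer that requiring both wins removes every need for multiplicity control. That holds within one outcome. With three primary outcomes and success on any one allowed, the false claim rate when FBT-HT equals one comparator and is far ahead of the other is about 6 to 7%, against 2.5% for one outcome (normal approximation, correlations of 0 to 0.5 assumed). If all three must succeed, power is below the per-outcome figure.
- A reader might infer that the 12-month results must become secondary. The plan includes follow-up in the primary analysis; demoting it would be a design preference.

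**Conclusion.** The point holds. The sample size of 66 is arithmetically right for the omnibus interaction on a single outcome and wrong as a statement about the main hypothesis. Under the plan's own f and r, no pattern reaches 80% for beating both arms with Tukey, even if all 90 patients complete. The omnibus result also cannot tell the hypothesised pattern from one in which FBT-HT is no better than FBT-MBSR, since both give 82%.

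The figures assume f = 0.2 as defined for the interaction, r = 0.5, equal arms, normally distributed outcomes, a two-time-point comparison and one outcome. The position of FBT-MBSR is not given in the protocol, so equal comparators and halfway are shown as a range.

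**What to change.** - State in the Power analysis section that the 80% at 66 completers applies to the omnibus interaction on a single outcome.
- Pre-specify two contrasts at week 12, the post-treatment time point that matches the two-time-point calculation: FBT-HT minus FBT and FBT-HT minus FBT-MBSR, each adjusted for the baseline value of the outcome.
- Claim superiority over both arms on a given outcome only if both contrasts favour FBT-HT with two-sided p < 0.05. No adjustment is needed across these two contrasts within one outcome.
- Set separately the rule for combining BMI, EDE and EDI-2.
- Restate the per-outcome power at 66 completers: about 81% if the comparators are equal and about 44% if FBT-MBSR is halfway.
- Report FBT versus FBT-MBSR as a secondary comparison. The 12-month results can stay in the analysis.

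The cost is rewording two paragraphs, with no added patients or data. The downside is that the stated power becomes less favourable when FBT-MBSR is intermediate: the new contrasts double it from 22% to 44% but do not bring it to 80%.

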### Data analysis plan

The initial descriptive statistics will summarize participant data characteristics as means, standard deviations, minima, maxima, frequencies and percentages. The validity of stratified randomization will be evaluated by inspecting between-group differences at baseline by means of a one-way analysis of variance (ANOVA), Kruskall–Wallis test or chi-squared test (in dependency of conventional statistical assumptions and the variable type, i.e., continuous versus categorical). Outcome data will be evaluated for the normality assumption by a combination of visual (Q–Q plots, histograms) and statistical (Shapiro–Wilk test) methods and will be transformed if necessary to meet the normality assumption. Participant characteristics of the analyzed sample and dropouts will be subjected to an additional inspection for possible non-random differences. Missing data will be handled by the maximum likelihood estimation method. The effects of the interventions will be assessed as changes in the primary outcomes from pre-test to post-test and follow-up assessment using EDE, EDI-2 and BMI analyzed with a repeated measures ANOVA followed by a post-hoc Tukey’s test to compare treatment means when there is a significant effect. The potential influence of confounding factors (age, premorbid BMI, duration of illness, age at onset, duration and setting of pre-treatment, medication use) will be further explored in sensitivity analyses. The secondary continuous variables will be analyzed in parallel. The measures related to treatment implementation (FBB, BPT) will be evaluated using descriptive statistics. Corrected effect sizes, expressed as Hedges’s *g* and significant deviations beyond the 95% confidence interval, will be computed for between- and within-group terms and will indicate empirical power estimates for a subsequent confirmatory study. Exploratory analyses will test the FB-K measure as a mediator/moderator of efficacy. To examine the FBT process, the ratings of each therapy session by the adolescents and the therapists will be compared and analyzed to assess their common development over time. More advanced statistical methods, such as generalized estimating equations (GEE) (which allow for more flexible modelling of the correlation structure among observations, are less sensitive to violation of assumptions and estimate population-wide average effects) will be also applied to assess differences in BMI percentiles and EDE/EDI-2 trajectories. The statistical significance threshold will be set to *p* < 0.05.

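### The primary analysis uses the baseline score only as a repeated measure; adjusting for it as a covariate would cut error variance by 25% at the plan's own r = 0.5

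*Protocol article*

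**What the plan says.** **Primary model (Data analysis plan).** The three primary measures (EDE, EDI-2, BMI) are assessed as change from the pre-treatment score to the later assessments, by repeated measures ANOVA, with Tukey comparisons after a significant effect. No baseline covariate is named. Age, premorbid BMI, illness duration and similar factors "will be further explored in sensitivity analyses"; the baseline value of the outcome is not in that list. GEE is an additional method.

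**Sample size (Power analysis).** The total of 66 is for a test "involving three groups, two time points and the statistical interaction term", with f = 0.2, 80% power, a 5% level and "correlation among repeated measures of *r* = 0.5". It is raised to 90 for 25% attrition.

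**Baseline comparability (Data analysis plan).** "The validity of stratified randomization will be evaluated by inspecting between-group differences at baseline by means of a one-way analysis of variance", or by a Kruskal–Wallis or chi-squared test depending on the variable. This is the article's only mention of stratification, and no factors are named.

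**Timing (Procedures).** Families learn after randomisation which add-on they will receive. The link to the questionnaires goes out after the initial interview, with seven days to complete them.

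**The concern.** With two time points, the group-by-time F test in a repeated measures ANOVA is the same test as a one-way ANOVA on change scores. A change score subtracts the whole baseline value, whereas the best linear prediction from baseline subtracts only r times it (equal variances at both times). Unless r is close to 1, the change score therefore over-corrects. This has two consequences:

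- The error variance is larger than it need be.
- A chance difference between arms at baseline stays in the estimated effect, with its sign reversed.

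Both matter in a trial of 30 per arm whose size, by the Power analysis, is close to what the clinic can recruit in three years. Extra precision has to come from the analysis.

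The baseline tests do not help. If allocation was properly random, any baseline difference is due to chance. At the 5% level such tests flag about 1 variable in 20 under correct randomisation, and with 30 per arm they can miss an imbalance large enough to matter. They neither establish that randomisation was sound nor correct an imbalance.

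**Working it through.** **Inputs** (Power analysis): k = 3 groups, m = 2 time points, f = 0.2, α = 0.05, r = 0.5, N = 66 before attrition. σ² is the variance of the outcome at one time, taken as equal at both.

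**1. Reproduce the plan's figure.** Noncentral F for the within-between interaction:

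- λ = f²·N·m/(1 − r) = 0.04 × 66 × 2/0.5 = 10.56
- df1 = (k − 1)(m − 1) = 2; df2 = (N − k)(m − 1) = 63
- Power = 81.8%

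The smallest N in equal arms with at least 80% power is 66, so the figure reproduces. For attrition, 66/0.75 = 88, so 90 is enough.

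**2. Error variance under the two analyses.**

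- Change score: 2σ²(1 − r) = 2 × 0.5 = 1.00σ²
- Baseline as covariate: σ²(1 − r²) = 1 − 0.25 = 0.75σ²
- Ratio: (1 + r)/2 = 0.75, a 25% reduction

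**3. Effect on power and size.**

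- λ = 10.56/0.75 = 14.08 with df 2 and 62; power at N = 66 is 91.7%
- N in equal arms for 80% power falls from 66 to 51
- With 8 further degrees of freedom spent on other terms, power is still 91.5%
- Efficiency of the change score is 0.75. To match 66 adjusted completers it needs 66/0.75 = 88. This equals the attrition-inflated figure in step 1 only by coincidence.

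A simulation (4,000 runs, 22 per arm, r = 0.5) gave residual variance 0.998 against 0.749 and power 81.7% against 91.2%.

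**4. Range over r.** The documents give only r = 0.5; the other values are assumptions. N = 66, with f = 0.2 held fixed.

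| r | Change score | Covariate | Reduction | Power, change | Power, covariate |
|---|---|---|---|---|---|
| 0.3 | 1.40σ² | 0.91σ² | 35% | 66.8% | 85.4% |
| 0.5 | 1.00σ² | 0.75σ² | 25% | 81.8% | 91.7% |
| 0.7 | 0.60σ² | 0.51σ² | 15% | 96.5% | 98.4% |
| 0.8 | 0.40σ² | 0.36σ² | 10% | 99.7% | 99.9% |
| 0.9 | 0.20σ² | 0.19σ² | 5% | >99.9% | >99.9% |

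The gain is largest where r is below the planned value and the change score test falls short of 80%.

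**5. Chance imbalance.** With 22 completers per arm, the standard error of a baseline difference between two arms is √(2/22) = 0.30 SD. The change score over-corrects by (1 − r) times the difference. At r = 0.5, an imbalance of one standard error shifts the estimate by 0.5 × 0.30 = 0.15 SD.

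**The case against.** The strongest reply is that nothing here is wrong. Under randomisation the change-score comparison is unbiased, the model matches the sample size calculation, 66 reproduces, and power already exceeds its target. That stands: the point concerns efficiency. It is still worth making, because the alternative uses data already scheduled in Table 1 at a cost of one degree of freedom.

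A second reply is that 25% belongs to one value of r and one pre-post contrast, while there are three primary measures and a later follow-up. That also stands. If BMI tracks at r = 0.8, the reduction is about 10%, and the absolute gain in power is then negligible.

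Four stronger readings are tempting but not supported:

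- **The analysis ignores the randomisation strata.** The described model has no stratum term, but this is a condensed article that never names the factors. The full protocol or SAP may include them. The 25% comes from baseline adjustment alone; no gain from stratum terms can be calculated here. A stratum effect that is equal at both times cancels from a change score anyway.
- **A third of the sample is wasted.** Matching the adjusted analysis takes a third more participants (88/66), but the share lost is a quarter (1 − 66/88).
- **The gain carries over to a stated power for FBT-HT to beat both comparators.** That needs a pattern of arm means and planned contrasts. The plan gives only f and specifies an omnibus test followed by Tukey.
- **The change is only a matter of wording.** If baseline questionnaires are now completed after families know their arm, correcting that is a change of procedure.

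**Conclusion.** The point holds as a loss of efficiency in a valid analysis. At the plan's r = 0.5, using the baseline score as a covariate rather than as a repeated level cuts error variance by 25% and raises power at 66 completers from about 82% to 92%. The planned test thus gives up about a quarter of the effective sample. It also leaves chance baseline imbalance in the estimate.

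The figures assume equal variances at the two times, a linear relation with baseline, the plan's f = 0.2 and a single pre-post contrast. The reduction, (1 − r)/2, runs from 35% at r = 0.3 to 10% at r = 0.8.

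Separately, the baseline significance tests cannot do what the plan asks of them. The Procedures section also leaves open whether the self-reported baseline scores precede knowledge of allocation. A covariate should be measured before it can be influenced by allocation, so this needs settling. The documents do not establish that baseline scores are in fact affected.

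**What to change.** 1. **Primary model.** For each primary measure, take the week 12 and 12-month scores as outcomes, with the participant's own baseline score as covariate and terms for arm, time and arm by time. A likelihood-based mixed model fits the maximum likelihood handling of missing data already stated. Between-arm comparisons are then made on adjusted means.
2. **Strata.** If the full protocol confirms stratified randomisation, name the factors and include them in the model.
3. **Other covariates.** Leave the listed confounders in the sensitivity analyses.
4. **Baseline table.** Remove the baseline hypothesis tests and present descriptive statistics by arm.
5. **Timing.** State in Procedures whether the baseline questionnaires are completed before the allocation is disclosed.

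**Cost.** Items 1 to 4 are changes to the analysis text. They use baseline scores already collected and a few degrees of freedom (power stays at 91.5% with 8 beyond the baseline term). The sample size can stay at 90. Item 5 costs one sentence if questionnaires already precede disclosure; otherwise it means a change to study procedures.
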